### Statistical Analysis

Analyses will be performed according to an intention-to-treat principle. Baseline characteristics and gait parameters will be descriptively summarized using either means and standard deviations or frequencies and percentages, as appropriate. Comparisons of the changes in the mean balance confidence score will be assessed using *t*-test. The coefficient of variation [CoV = (SD/mean)*100] will be used to quantify gait variability. We will use linear regression to perform between-group comparisons using three data points (baseline, one month, six months) with baseline – 1 mo. corresponding to before treatment and 1 mo. – 6 mo. corresponding to treatment with donepezil. Linear regression models, both unadjusted and adjusted for age, sex, and history of falls, will be used for comparison of individual variables. Using the baseline value of an endpoint as a covariate is more powerful statistically than comparing the differences from baseline. The statistical significance of the results will be determined by Hochberg's variation of the Bonferroni procedure for multiple testing [65]. Two-sided *p *< 0.05 will be considered statistically significant. All calculations will be made using SPSS software package version 16.0 (SPSS Inc., Chicago, IL).

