#### Secondary outcomes

Between-group improvement in:

1. Balance confidence as evaluated by the Activities-Specific Balance Confidence Scale (ABC)

2. Balance sway, maximum saggital displacement, using a force platform (Bertec Inc.)

3. Attention measured with the Digit Span Test

4. Executive function using the Trail Making Test, parts A and B

5. Reduction of number of falls: The total number of falls by month 6 (T2) and proportion of participants who fall are also secondary outcome measures to be evaluated.

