### Randomisation

Once informed consent has been obtained and the baseline assessment has been completed, participants will be allocated to one of the two arms at a ratio of 1:1. Stratified randomization within strata based on fall history (0 falls, 1+ fall in past 12 months) will be performed. A block randomization by four will be applied to ensure a cumulative balance of participants between arms. The randomization sequence of the participants will be generated by a computer program and allocation to groups will be done with sequentially numbered opaque sealed envelopes. A professional bio-statistician not involved in recruitment and assessment will perform the randomization

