### Sample size determination

Sample size determination is based on our primary outcomes and using the values from the pilot data described above. We expect a 10% improvement in gait velocity (G-vel), measured in cm/s (effect size of 0.10 m/s, from 1.0 m/s to 1.10 m/s), and a reduction in gait variability (G-var) (stride time variability) of 10% as assessed by decreases in standard deviation and coefficient of variation. These expected changes are based on our preliminary data which showed that mean G-vel increased by 15% after one month of treatment and these changes were sustained and improved in the 4 months follow up [38]. In this study, we found that the mean stride time at usual gait was 1190 ± 266 milliseconds (ms), after one month of treatment was 1053 ± 178 ms, and after 4 month was 999 ± 112 ms. The absolute reduction of the mean group CoV was 11 points (from 22.4% to 11.3%). Therefore, it is reasonable to expect similar improvements in our proposed study with a larger sample. Thus, in order to detect a group reduction of variability of 10% with a type II error of 0.20, 69 participants in each arm will be needed for the final analysis; assuming a 5 percent drop-out rate (which was seen after 6 months in two previous studies testing medications on MCI), 75 per arm participants will need to be recruited. This sample will also allow the detection of a 10% difference in the mean scores of the ABC, which is considered clinically significant. While we will not have sufficient power for a definitive analysis of changes in fall rate or risk, we will be able to compare changes in the mean values of the primary outcomes with between-group differences in fall rate. This will add mechanistic evidence that changes in fall rate are due to changes in gait parameters, and will provide a point estimate needed for the sample size calculations for a future trial powered to detect a reduction in falls as a primary endpoint.

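### Balance confidence is to be tested by a t-test on change from baseline, although the same paragraph rates baseline adjustment as more powerful; the adjusted models do not name the baseline value

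*Protocol article*

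**What the plan says.** Four statements bear on this point. The first three stand in one paragraph of the protocol article, under Statistical Analysis.

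- ABC: "Comparisons of the changes in the mean balance confidence score will be assessed using" a t-test. The visit is not named; I take the change to be from baseline to month 6.
- Regression models: "We will use linear regression to perform between-group comparisons using three data points (baseline, one month, six months"), followed by "Linear regression models, both unadjusted and adjusted for age, sex, and history of falls, will be used for comparison of individual variables".
- Directly after the covariate list: "Using the baseline value of an endpoint as a covariate is more powerful statistically than comparing the differences from baseline".
- Under Randomisation: "Stratified randomization within strata based on fall history (0 falls, 1+ fall in past 12 months) will be performed".

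ABC is listed first among the secondary outcomes. The Sample size determination section says that the sample will also detect a 10% difference in mean ABC, but gives no SD for ABC. Significance is to be judged by Hochberg's procedure. The paragraph does not say whether the unadjusted or the adjusted p-value enters it.

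**The concern.** The plan states a principle and then, for ABC, does the opposite: it compares differences from baseline after saying that a baseline covariate is more powerful. For the other endpoints it lists the adjustment covariates without the one that the principle recommends, so the text does not settle whether baseline enters those models.

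Three things are at stake, all modest:

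- Precision on ABC, an outcome for which the plan makes an explicit detection claim.
- Clarity about the model for the other continuous endpoints, including the primary gait outcomes at month 6.
- The input to Hochberg's procedure, which needs one p-value per hypothesis while two models per variable are planned.

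**Working it through.** **The plan's own figure.** The document gives no precision or power figure for the ABC comparison, so there is none to reproduce. The nearest figure is "with a type II error of 0.20, 69 participants in each arm will be needed for the final analysis", which is for gait variability. It does not follow from the printed pilot values. For example, 10% of the mean stride time of 1190 ms is 119 ms, and with SD 266 ms, two-sided 0.05 and 80% power, n = 2 × 2.802² × (266/119)² = 79 per arm. The SD of the coefficient of variation, which is the input needed, is not printed, so this does not show 69 to be wrong. It has no bearing on the present point. I use 69 below only as a sample size for illustration.

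**Inputs.** Two arms, 1:1 (Randomisation); 69 per arm (Sample size determination); two-sided 0.05 (Statistical Analysis). The correlation r between baseline and month 6 is not given and is varied from 0.3 to 0.9. The SD s is assumed equal at both visits.

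**Formulas** (variance per participant that drives the standard error of the arm difference):

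- Change score: 2(1 − r)s²
- Baseline-adjusted (ANCOVA): (1 − r²)s²
- Ratio: (1 − r)(1 + r) / [2(1 − r)] = (1 + r)/2

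Equal SDs are not needed for the direction. With SDs s₀ at baseline and s₁ at month 6, the change-score variance minus the ANCOVA variance is s₀² + s₁² − 2r·s₀·s₁ − (1 − r²)s₁² = (s₀ − r·s₁)², which is never negative. The plan's own statement about power is therefore correct.

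**Illustration.** To show the scale, take the standardised difference that 69 per arm detects with 80% power: d = (1.960 + 0.842) × √(2/69) = 0.477. This is solved back from 69; it is not an ABC value.

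| r (assumed) | Variance ratio | Power, change | Power, ANCOVA | n per arm for 80%, change | n per arm for 80%, ANCOVA |
|---|---|---|---|---|---|
| 0.3 | 0.65 | 65.8% | 83.6% | 97 | 63 |
| 0.5 | 0.75 | 80.0% | 89.9% | 69 | 52 |
| 0.7 | 0.85 | 95.1% | 97.5% | 42 | 36 |
| 0.8 | 0.90 | 99.3% | 99.7% | 28 | 25 |
| 0.9 | 0.95 | about 100% | about 100% | 14 | 14 |

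For r from 0.5 to 0.8 the gain equals 25% down to 10% fewer participants for the same precision. Confidence intervals would be 13% down to 5% narrower (1 − √0.75 and 1 − √0.90).

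**Covariates.** The three sentences on regression mention baseline twice: once as one of three data points, and once in the general remark on power. Neither says that it is a term in a model. The one explicit list has age, sex and history of falls.

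**The case against.** The strongest reply is that the power sentence comes directly after the covariate list and has little purpose there except to justify baseline-adjusted regression. A reader might infer that the plan leaves baseline out of every model, the primary gait models included. The text does not support that: it fails to name baseline but never excludes it, and a journal article often leaves exact model terms to a fuller document. What stands is that the term should be written down. This reading does not rescue the ABC test, which remains the method that the sentence ranks lower. ABC might also be covered by the regression for individual variables, but then it has two tests with no stated priority.

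Other stronger readings also fail.

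- A reader might call the t-test on change biased or liable to false positives. Under 1:1 randomisation it is unbiased, and ignoring the stratum makes it, if anything, conservative.
- A reader might say that the plan ignores the randomisation stratum. The adjusted models include history of falls; only the t-test and the unadjusted models leave it out. For a change score, the stratum matters only if fall history predicts change in ABC, and no figure in the document bears on that.
- A reader might measure the gain against an analysis that uses no baseline information and quote a much larger saving. The plan does not clearly state such an analysis.
- A reader might suspect that the better of two p-values will be picked. Nothing says so, and reporting both models is ordinary. But Hochberg's procedure does not itself settle which one counts.

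**Conclusion.** The point holds in a limited form. The ABC test conflicts with the plan's own statement on power, and the covariate list does not name the endpoint's baseline value, although it may be implied. The planned test is valid; the loss is precision on a secondary outcome. On the formula above, the baseline-adjusted variance is 0.75 to 0.90 of the change-score variance for an assumed r of 0.5 to 0.8, and there is almost nothing to gain when r is near 1. The true size for ABC cannot be fixed, because the document gives neither r nor an SD for that scale. This is a free improvement, not a threat to the trial's conclusions.

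**What to change.** 1. Replace the t-test on change in ABC with a linear model of the month-6 ABC score on arm, baseline ABC and the fall-history stratum, plus age and sex as already planned.
2. Add the endpoint's baseline value by name to the covariates of the adjusted regression models for the other continuous endpoints, including the month-6 gait comparison. The three-visit regression need not be given up. The text should only say how baseline is used, so that it does not serve as both response and covariate.
3. State that the adjusted model supplies the p-value that enters the Hochberg procedure, with unadjusted results as sensitivity analyses.

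The cost is wording. The baseline assessment is completed before allocation and the stratum is known at allocation, so no further data or participants are needed.

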### Measurements and Procedures

All participants will undergo a baseline, one month, and a final six-month assessment. Baseline gait assessment will occur within one week prior to starting donepezil (T0), with a second assessment occurring after 4 weeks of treatment at 5 mg of medication (T1). The third and final assessment will occur after participants have been on the full dose of donepezil, 10 mg, for a period of 5 months (T2), yielding a total period of follow-up of 6 months from baseline. Assessments at each of these time-points will include gait analysis, balance sway, and balance confidence as well as cognitive measurement of attention and executive function. Falls will be retrieved by phone interview as has been done in previous studies [47,48]. A timeline for the proposed study can be found in Figure 4.

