#### Hypothesis and Objectives

• **Hypothesis 1: **Cognitive enhancers reduce fall risk in elderly people with MCI by improving their gait performance.

• **Hypothesis 2: **Cognitive enhancers improve balance and balance confidence in elderly people with MCI.

• **Mechanistic Hypothesis: **The improvement on gait and balance measures is due to an enhancement in attention and executive function.

• **Objective 1: **To assess the effect of donepezil on gait velocity and gait variability in elderly people with MCI using an electronic walkway (Gait Rite System, CIR Systems Inc.).

• **Objective 2: **To evaluate the effect of donepezil on balance and in balance confidence in elderly people with MCI using a balance platform (Bertec Inc.) and the Activities-Specific Balance Confidence Scale (ABC).

• **Objective 3: **To test if these potential improvements on gait and balance are mediated through an enhancement in attention and executive function.

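### The only test named specifically for balance confidence (ABC) is a t-test on changes, although the same section says that adjusting for baseline is more powerful; the cost is precision on one secondary outcome

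*Protocol article*

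**What the plan says.** ABC is the first secondary outcome in the protocol article ("Balance confidence as evaluated by the Activities-Specific Balance Confidence Scale (ABC") and part of Objective 2: "To evaluate the effect of donepezil on balance and in balance confidence in elderly people with MCI". It is measured at baseline, one month and six months; Measurements and Procedures says "Assessments at each of these time-points will include gait analysis, balance sway, and balance confidence".

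The Statistical Analysis section contains three statements that bear on it:

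- For ABC by name: "Comparisons of the changes in the mean balance confidence score will be assessed using" a t-test.
- For outcomes in general, linear regression using the three visits, with models "both unadjusted and adjusted for age, sex, and history of falls, will be used for comparison of individual variables". The variables covered are not listed.
- Directly after that: "Using the baseline value of an endpoint as a covariate is more powerful statistically than comparing the differences from baseline".

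Significance is judged by Hochberg's procedure at a two-sided 0.05 level. Under Randomisation the article says: "Stratified randomization within strata based on fall history (0 falls, 1+ fall in past 12 months) will be performed".

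**The concern.** The one method tied to ABC by name compares changes from baseline. A few sentences later the section says that this approach has less power than using the baseline value as a covariate. No reason is given for treating ABC differently, and the baseline score will be in hand for everyone randomised, because allocation follows the baseline assessment.

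The regressions do not clearly repair this. ABC may or may not be among the variables they cover, and the covariates listed are age, sex and history of falls, not the baseline value of the endpoint. A two-sample t-test also cannot include the fall-history stratum.

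At stake is a wider confidence interval than necessary for the ABC effect. If ABC is analysed both ways, it is also unclear which p-value enters the Hochberg procedure.

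**Working it through.** **Inputs from the article.** 69 analysed per arm and type II error 0.20 (Sample size determination, stated for gait variability); two-sided 0.05 (Statistical Analysis); 1:1 allocation (Randomisation).

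**Not in the article.** The mean and SD of ABC, and the correlation r between baseline and month-6 ABC. Values of r from 0.5 to 0.9 are assumed below.

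**The article's own ABC figure.** Sample size determination says "This sample will also allow the detection of a 10% difference in the mean scores of the ABC". The standardised difference detectable with 69 per arm at 80% power is (1.960 + 0.842) × √(2/69) = 0.477. A 10% difference would therefore need an SD of about 0.10/0.477 = 21% of the mean. With no ABC mean, SD, correlation or test stated, the claim cannot be reproduced, and nothing below depends on it.

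**Variance of the two analyses.** Let s0 and s6 be the baseline and month-6 SDs within arm. Per participant:

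- Change score: s0² + s6² − 2·r·s0·s6.
- Baseline-adjusted: s6²(1 − r²).
- The change-score variance exceeds the adjusted variance by s0²(1 − b)², where b = r·s6/s0 is the regression slope on baseline.

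Apart from the small cost of estimating the slope, adjustment is never worse. The two are equal when b = 1.

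**Equal SDs (s0 = s6 = s).** The change score has variance 2s²(1 − r) and the adjusted analysis s²(1 − r²). The ratio of adjusted to change-score variance is (1 + r)/2.

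**Power.** Suppose the change-score test has exactly 80% power at 69 per arm. The adjusted analysis then has power Φ(2.802/√((1 + r)/2) − 1.960). The participants per arm that it needs for 80% power are 69 × (1 + r)/2, rounded up.

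| r (assumed) | Variance ratio (1+r)/2 | Power, change score | Power, adjusted | Per arm for 80%, adjusted |
|---|---|---|---|---|
| 0.5 | 0.75 | 80% | 90% | 52 |
| 0.7 | 0.85 | 80% | 86% | 59 |
| 0.8 | 0.90 | 80% | 84% | 63 |
| 0.9 | 0.95 | 80% | 82% | 66 |

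Conversely, for the change-score test to match the adjusted precision, the total of 138 would have to grow to 138/0.75 = 184 at r = 0.5 (46 more), about 162 at r = 0.7 (24 more) or about 153 at r = 0.8 (15 more).

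**Simulation check** (4,000 runs, 69 per arm, equal SDs). Power was 0.79, 0.79 and 0.78 for the t-test on changes, and 0.89, 0.86 and 0.80 for the adjusted regression, at r = 0.5, 0.7 and 0.9.

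**Unequal SDs.** With r = 0.8 and s6/s0 = 1.25, b = 0.8 × 1.25 = 1. In units of s0², the change-score variance is 1 + 1.5625 − 2 = 0.5625 and the adjusted variance is 1.5625 × 0.36 = 0.5625. The gain is then nil.

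**The case against.** The strongest reply is that the regressions are described in general terms and may well include ABC. The t-test would then be a simple first comparison, and the remark about baseline as a covariate would state how the regressions are meant to be run. A reader might infer that the regressions are reserved for the other outcomes and that ABC is deliberately given the weaker method. The text does not say that. Nor does it say that ABC is included, and baseline is not among the listed covariates. The ambiguity stands, and so does the need to name one ABC analysis. The complaint about the fall-history stratum applies only if ABC lies outside those regressions, since they do list history of falls.

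A reader might also infer that the statement about detecting a 10% ABC difference rests on the change-score test. The documents do not support this: that statement refers to mean scores and gives no test, SD or correlation.

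A third tempting reading is that the change-score test is biased. It is not: under randomisation it is unbiased over repeated trials and holds its type I error. Only conditionally on a chance baseline gap does it favour the arm that starts lower. With equal SDs the shift is gap × (1 − r), so a 0.2 SD gap gives 0.04 SD at r = 0.8 and 0.10 SD at r = 0.5. The SE of the baseline difference is √(2/69) = 0.170 SD, so a gap of at least 0.2 SD in either direction has a probability of about 24%.

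Finally, the power gain rests on an assumed r and on an 80% starting point borrowed from gait variability. If ABC power is already well above 80%, the gain is smaller. That is correct and limits the size of the point.

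**Conclusion.** The point holds as a matter of efficiency and clarity. The only method named for ABC is one that the same section describes as less powerful, and it is not stated that the regressions cover ABC or adjust for its baseline. The t-test remains valid, and the primary gait outcomes do not depend on it.

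The loss is moderate at r = 0.5 to 0.7 (change-score variance 33% to 18% higher than adjusted, from 1/0.75 and 1/0.85) and small at r = 0.9 (5%). These sizes assume equal baseline and month-6 SDs and an r that the article does not give; the power figures also assume 80% power for the change-score test. The loss shrinks to nothing as the regression slope on baseline approaches 1. Baseline adjustment still has essentially no downside, so the case for changing the analysis does not depend on the missing figures.

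**What to change.** In Statistical Analysis, replace the t-test sentence with wording such as:

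*Month-6 ABC will be compared between arms by linear regression on arm, baseline ABC and fall-history stratum; the p-value from this model is the one that enters the Hochberg procedure. Age and sex are added in the planned adjusted model.*

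Keep the mean change per arm as description; the one-month ABC values can be described alongside it. Month 6 matches the time point of the primary outcomes.

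The cost is one replaced passage of text. No new data, visits or participants are needed, and the planned age and sex adjustment is retained.

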### Outcomes measures

#### Primary outcomes

1. Improvements in gait velocity (cm/second) at month six

2. Reduction in gait variability assessed as standard deviation (SD) and coefficient of variation (CoV) at month 6.

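### The only between-group model given for the gait outcomes is a three-visit linear regression that does not fit the month-6 primary outcomes and, if run literally on stacked visits, has invalid standard errors

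*Protocol article*

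**What the plan says.** Measurements and Procedures sets three visits: "All participants will undergo a baseline, one month, and a final six-month assessment". It describes the one-month visit as follows: "with a second assessment occurring after 4 weeks of treatment at 5 mg of medication (T1").

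Primary outcomes places both outcomes at the last visit: "Improvements in gait velocity (cm/second) at month six" and "Reduction in gait variability assessed as standard deviation (SD) and coefficient of variation (CoV) at month 6".

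Statistical Analysis then makes four statements about the model:

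- The method: "We will use linear regression to perform between-group comparisons using three data points (baseline, one month, six months").
- The sentence continues with a label for each interval: "with baseline – 1 mo. corresponding to before treatment and 1 mo. – 6 mo. corresponding to treatment with donepezil".
- The covariates: "Linear regression models, both unadjusted and adjusted for age, sex, and history of falls, will be used for comparison of individual variables". The baseline value of the outcome is not in this list.
- A general remark: "Using the baseline value of an endpoint as a covariate is more powerful statistically than comparing the differences from baseline". It is tied to no model and no visit.

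The only other between-group test named is a *t*-test for change in balance confidence, a secondary outcome. The regression is therefore the only between-group model given for gait velocity and gait variability. No random effect, repeated-measures covariance, estimating-equation method or robust standard error is mentioned.

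**The concern.** Three gait measurements on one person are correlated, and ordinary linear regression takes its errors as independent. If the three visits are entered as three rows per person, the reported standard error is not the true one. The direction of the error depends on the term tested. A constant arm effect gets a standard error that is too small, and an arm-by-time term gets one that is too large. The Hochberg adjustment cannot repair this, because it takes valid p-values as its input.

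The estimand also suffers. Baseline precedes treatment, so its expected arm difference under randomisation is zero. An arm effect averaged over three visits that include baseline is not the month-6 effect named as primary.

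Finally, the section's own statements point to different analyses. An analyst could choose among them after seeing data, and their error rates differ widely.

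**Working it through.** **Inputs.** From the document: three visits, 1:1 allocation, 69 analysed per arm, two-sided 5% level, and a planned velocity effect of 10 cm/s (1.0 to 1.10 m/s). The within-person correlation ρ is not given. I assume 0.3 to 0.9, with equal variances and the same correlation between every pair of visits. The plan states no figure on this point to reproduce; 69 per arm is used only as the simulated size.

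**Step 1. Formulas for stacked rows.** With variance σ² and n per arm:

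- Constant arm effect over three visits: true variance 2σ²(1+2ρ)/(3n), ordinary-regression variance 2σ²/(3n). The ratio of true to reported standard error is √(1+2ρ).
- Arm-by-time contrast (month 6 minus baseline): true variance 4σ²(1−ρ)/n, ordinary-regression variance 4σ²/n. The ratio is √(1−ρ).
- Actual type I error is 2[1 − Φ(1.96/ratio)].

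| ρ | Ratio, constant effect | Type I error | Ratio, arm-by-time | Type I error |
|---|---|---|---|---|
| 0.3 | √1.6 = 1.26 | 12.1% | √0.7 = 0.84 | 1.9% |
| 0.5 | √2.0 = 1.41 | 16.6% | √0.5 = 0.71 | 0.6% |
| 0.7 | √2.4 = 1.55 | 20.6% | √0.3 = 0.55 | 0.03% |
| 0.9 | √2.8 = 1.67 | 24.1% | √0.1 = 0.32 | <0.001% |

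**Step 2. Simulation under no effect.** 69 per arm, 5,000 runs per setting, conventional standard errors. The Monte Carlo standard error near 5% is √(0.05×0.95/5000) = 0.3 percentage points.

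| ρ | 3 rows, constant arm effect | 3 rows, arm-by-month-6 | 2 post-baseline rows, baseline covariate, constant arm effect | Same, visit-specific arm effect | Month-6 ANCOVA, one row per person |
|---|---|---|---|---|---|
| 0.3 | 12.3% | 2.0% | 7.5% | 4.7% | 4.7% |
| 0.5 | 16.0% | 0.6% | 9.0% | 5.2% | 4.7% |
| 0.7 | 20.9% | 0.0% | 9.6% | 4.9% | 4.5% |
| 0.8 | 21.7% | 0.0% | 9.9% | 5.0% | 4.6% |
| 0.9 | 24.6% | 0.0% | 10.6% | 4.8% | 5.0% |

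The visit-specific column was tested at month 1; month 6 is symmetric in this set-up. Simulation and formula agree.

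**Step 3. Dilution under a constant arm effect.** Let D be the month-6 effect and fD the month-1 effect, with f between 0 and 1. The average over three visits is (0 + fD + D)/3. That is D/3 if f = 0 and 2D/3 if f = 1. For D = 10 cm/s it estimates 3.3 to 6.7 cm/s.

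**Step 4. The interval reading.** If month 1 serves as the pre-treatment reference, the arm contrast of the later interval estimates D − fD = (1−f)D. Any effect already present at month 1 is removed. The document's pilot data make an early effect plausible: velocity went from 89.7 to 106.9 after one month.

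**Step 5. The statements side by side.**

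- Baseline as one of three data points, against baseline as covariate: one model cannot do both.
- Three data points, against primary outcomes at month 6 only.
- Baseline to one month as pre-treatment, against a one-month visit after four weeks of treatment.

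**The case against.** A reader might infer that the plan commits to ordinary regression on stacked rows, so that the p-values for the primary outcomes will be wrong. The document does not support that. It never says that rows are stacked or that a person's values are taken as independent, and it nowhere describes an arm effect averaged over visits including baseline. The remark on baseline as a covariate is the usual argument for ANCOVA. Together with month-6 outcomes it fits one row per person, where the simulated error is nominal. Even some stacked models, such as two post-baseline rows with visit-specific arm effects, come out nominal. The 12% to 25% range belongs to one model among several and to an assumed correlation. It is also fair to say that an article may leave the covariance structure to a full analysis plan, so that omission alone would be no finding.

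All of this stands against the stronger claim. It does not rescue the text. The covariate remark is attached to no model or visit, and the adjusted model lists age, sex and history of falls without baseline. To reach the valid month-6 analysis one must set aside the sentence that names the three data points. The interval reading does not help either, because its pre-treatment label conflicts with the visit schedule. The issue is statements that conflict, not detail left out.

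**Conclusion.** The point holds in conditional form. The plan's only stated between-group model for the primary outcomes is a three-visit linear regression that does not match the month-6 outcomes, conflicts with the baseline-covariate remark, and carries a period label that contradicts the visit schedule. If it were run literally on stacked rows, the standard errors would be invalid: type I error about 12% to 25% for a constant arm effect, and about 2% falling to 0% for an arm-by-time term. A month-6 ANCOVA gives 4.5% to 5.0%. The sizes rest on an assumed correlation of 0.3 to 0.9, equal variances and equal correlation between visits. The internal conflicts rest on the text alone.

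**What to change.** Replace the three-visit regression with one model whose arm difference at month 6 is the primary test. Either of these will do:

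- ANCOVA of the month-6 value on arm, baseline value and fall-history stratum, with age and sex added in the adjusted model.
- A mixed model for repeated measures on the one-month and six-month values, with baseline as covariate, arm, visit and arm-by-visit terms, fall-history stratum, and unstructured within-person covariance; age and sex added in the adjusted model. The month-6 contrast is the primary test.

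Reconcile the label on the baseline to one-month interval with Measurements and Procedures. The cost is a few sentences of analysis text and, for the mixed model, slightly more programming. No new data, visits or participants are needed.
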